# Impact of a health literacy intervention combining general practitioner training and a consumer facing intervention to improve colorectal cancer screening in underserved areas: protocol for a multicentric cluster randomized controlled trial

**DOI:** 10.1186/s12889-021-11565-3

**Published:** 2021-09-16

**Keywords:** Colorectal cancer screening, Health literacy, Intervention, General practitioner training, health disparities

## Abstract

**Background:**

Colorectal cancer (CRC) is a leading cause of cancer burden worldwide. In France, it is the second most common cause of cancer death after lung cancer. Systematic uptake of CRC screening can improve survival rates. However, people with limited health literacy (HL) and lower socioeconomic position rarely participate. Our aim is to assess the impact of an intervention combining HL and CRC screening training for general practitioners (GPs) with a pictorial brochure and video targeting eligible patients, to increase CRC screening and other secondary outcomes, after 1 year, in several underserved geographic areas in France.

**Methods:**

We will use a two-arm multicentric randomized controlled cluster trial with 32 GPs primarily serving underserved populations across four regions in France with 1024 patients recruited. GPs practicing in underserved areas (identified using the European Deprivation Index) will be block-randomized to: 1) a combined intervention (HL and CRC training + brochure and video for eligible patients), or 2) usual care. Patients will be included if they are between 50 and 74 years old, eligible for CRC screening, and present to recruited GPs. The primary outcome is CRC screening uptake after 1 year. Secondary outcomes include increasing knowledge and patient activation. After trial recruitment, we will conduct semi-structured interviews with up to 24 GPs (up to 8 in each region) and up to 48 patients (6 to 12 per region) based on data saturation. We will explore strategies that promote the intervention’s sustained use and rapid implementation using Normalization Process Theory. We will follow a community-based participatory research approach throughout the trial. For the analyses, we will adopt a regression framework for all quantitative data. We will also use exploratory mediation analyses. We will analyze all qualitative data using a framework analysis guided by Normalization Process Theory.

**Discussion:**

Limited HL and its impact on the general population is a growing public health and policy challenge worldwide. It has received limited attention in France. A combined HL intervention could reduce disparities in CRC screening, increase screening rates among the most vulnerable populations, and increase knowledge and activation (beneficial in the context of repeated screening).

**Trial registration:**

Registry: ClinicalTrials.gov.

Trial registration number: 2020-A01687-32.

Date of registration: 17th November 2020.

**Supplementary Information:**

The online version contains supplementary material available at 10.1186/s12889-021-11565-3.

## Background

Colorectal cancer (CRC) is a leading cause of cancer burden worldwide and the third most commonly diagnosed cancer in France. Its incidence is expected to increase by 60% to more than 2.2 million new cases and 1.1 million deaths by 2030. In France, it is the second most common cause of cancer death after lung cancer [1–3]. A mass CRC screening program was introduced in 2009. Research evidence confirms that completing a Fecal Immunochemical Test (FIT) and colonoscopy (when the FIT test result is positive) will reduce CRC related mortality [4, 5]. However, for the screening program to be effective, a 45% uptake rate is required [6, 7].

In France, the CRC screening program uptake continues to remain low (30.5% in 2018–2019), slow and socially graded [8–10]. It is significantly lower than European targets (at least 45%) [6, 7]. The national screening program, managed by regional cancer screening coordination centers (Centres Régionaux de Coordination des Dépistage des Cancers: CRCDCs) targets people between 50 and 74 years old. Standardized invitation letters are sent to eligible patients asking them to consult their general practitioner (GP) to obtain the testing kit and take the FIT test at home every 2 years. The testing kits can be given by a GP or a specialist (a gastroenterologist, gynecologist or a doctor working in French health insurance medical centers). Although the current uptake rate is only 30.5%, the objective of the French screening program is to achieve an uptake rate of between 45 and 65%. In France (as is the case worldwide), screening test uptake appears correlated with lower socioeconomic position, gender and age, with important geographic variations [8]. Screening uptake decreases with increasing levels of deprivation and is thus lower among underserved populations [11]. It is worth noting that in France and throughout Europe, high socioeconomic position, and specifically higher educational attainment, has a significant impact on reducing cancer mortality [12–14].

In this context, an important determinant of the socially graded uptake of CRC screening is health literacy (HL) [10]. HL is defined as “the degree to which individuals have the capacity to obtain, process and understand basic health information and services needed to make appropriate health decisions” [15]. HL includes: 1) basic skills in reading and writing, enabling individuals to understand health information and how to use the health system (functional HL); 2) the development of the patient’s skills in asking questions, communicating about one’s health and identifying knowledge gaps (communicative/interactive HL); and 3) the ability to make informed health decisions to appropriately manage one’s health and illness (critical HL) [16, 17]. Limited HL is associated with poorer health outcomes, poorer use of preventive health services (including cancer screening) higher burden of disease, poorer general health status, health resources use and higher mortality [18–27]. It disproportionately affects patients with financial deprivation, lower socioeconomic position, lower educational attainment and older age, thus suggesting a social gradient of HL [19, 22].

Growing research, primarily conducted in the US and UK, demonstrates the association between HL and CRC screening [27–31]. Limited HL is increasingly described as a barrier to CRC screening that significantly influences screening knowledge, beliefs and behavior [2]. People with lower HL are less likely to seek and understand information about CRC screening, and have lower self-efficacy for screening [31]. To improve outcomes and minimize health disparities, it is critical that people of lower HL and lower socioeconomic position are able to process health information, access and navigate the healthcare system to effectively manage their health and care [19, 22]. HL should be addressed and facilitated to improve equitable access to healthcare [32]. In the context of cancer prevention, addressing HL to help patients understand cancer screening can increase knowledge and screening uptake, limit social inequalities in screening and potential inequalities in survival [22, 32].

Disparities in CRC screening are widening. Physician communication to patients with limited HL skills (likely to be more socioeconomically disadvantaged) about CRC screening is often poorly understood and studied [30, 33]. GPs are frequently unaware of literacy/HL barriers that their patients may be facing. They often struggle to convey evidence-based information about CRC screening to those populations [33]. Our aim is thus to assess the impact of a HL intervention combining HL and CRC screening training for GPs with a brochure and video targeting eligible patients to increase CRC screening and improve other secondary outcomes (knowledge, patient activation, screening intention, decisional conflict, proportion of participants who complete a colonoscopy after a positive FIT test) in underserved areas of four different regions in France.

## Methods

The trial protocol follows the SPIRIT guidelines (see Additional file 1) and CONSORT statement for cluster randomized controlled trials [34, 35]. The three aims of our study are summarized in the context of the logic model shown in Fig. 1.

**Fig. 1 Fig1:**
[figure not shown]
Logic model of the intervention and study. Legend: TRAPD: Translation, Review, Adjudication, Pretest, Documentation

### Aim 1

To improve CRC screening uptake by addressing HL among underserved populations.

### Hypothesis 1.1

An interactive e-learning HL training for GPs targeting CRC screening combined with a patient-directed intervention (pictorial brochure and video) will increase CRC screening uptake (primary outcome), screening intention, knowledge, patient activation, decisional conflict and the proportion of patients who complete colonoscopy after a positive FIT test result within 1 year, among underserved populations eligible for screening.

### Hypothesis 1.2

The effect of the intervention on screening uptake and proportion of colonoscopy procedures completed will be mediated by post-intervention knowledge, patient activation and screening intention post consultation (see Fig. 2) after 1 year. HL level at baseline (T1) and socioeconomic position will affect screening uptake and moderate the intervention’s effect.

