### GP recruitment

To recruit GPs, we will first use a purposive sampling approach to include a balance of male and female GPs, practicing alone and in medical centers, in each region. GP work addresses will be coded against the EDI to establish if their practice covers a geographically disadvantaged area (EDI 4 or 5). GPs will be approached by email or telephone and given information about the trial. If this approach fails, we will transition to a convenience sampling approach, using contacts in our research network. Confirmation of participation will be by email and further contact details obtained. GPs will be randomly allocated to the control or intervention arm prior to the intervention training process, 2 months before patient recruitment begins. If a participating GP leaves their practice or decides to leave the trial, we will recruit another GP and assign him or her to the same arm.

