### Ethical approval, consent and recruitment strategies

The trial has received approval from the local research ethics committee, the Comité d’Ethique de la Recherche (CER) at the University of Toulouse III Paul Sabatier, France (ref 2021–349, dated 8th March 2021). Eligible participants will be asked to read a brief information sheet written in plain language or have a resident, mediator/patient navigator or other member of medical staff read the information out loud to them. This is particularly relevant since participants targeted by the trial are likely to have lower HL and lower textual literacy. According to the French health research classification, the ethics committee’s requirement for consent for this study requires participants’ verbal consent only or ‘non-opposition’ consent. Participants recruited by an intervention GP will be given a pictorial brochure about CRC screening and asked to watch a 3-min video on a tablet before exiting the primary care center/GP’s office. Participants recruited by a GP in the control arm will discuss the trial and CRC screening in their usual way.

One week after (T1), the CRA will call participants and offer to conduct a standardized telephone interview where the questions will be read out loud to them. Whenever possible, T1 data collection will be carried out in a single phone call. If the participant does not answer the first telephone call, the CRA will make three further attempts to contact them and leave up to three voice messages. CRAs will verify telephone contact details with the recruiting GP practices. Given participants are likely to have lower HL, this is the best strategy to maximize retention and minimize participant burden and missing data.

One year after (T2), CRAs will call participants for the follow-up assessment and offer to conduct a further standardized telephone interview. As with T1, attempts to verify contact details and to call the participant several times will be made.

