### Outcome measures

#### Primary outcome measure

The primary outcome measure is CRC screening uptake assessed 1 year after the initial recruitment consultation (T2) by self-report questionnaire (see Table 1). Each CRCDC, in collaboration with the health insurance body (CPAM) in each region, will also provide data on CRC screening uptake at 6 months (for feedback to GPs in the intervention arm) and 1-year post enrollment.

**Table 1 Tab1:** Outcome measures and data collection timepoints for patients

Outcome measures	Timepoints	
	(T1) One week after the primary care consultation where CRC screening is discussed	(T2) 1 year after the CRC screening consultation
Number of eligible patients identified and successfully enrolled	**X**	
Number of patients enrolled who receive the patient-facing intervention	**X**	
Discontinuation rate		**X**
CRC screening uptake (primary outcome) with self-report item		**X**
Screening intention (1 items)	**X**	
Knowledge of CRC screening (2 items)	**X**	**X**
Patient activation (13 items)	**X**	**X**
Health literacy (7 items)	**X**	
EPICES (11 items)	**X**	
SURE (4 items)	**X**	
Was the questionnaire completed alone? (1 item)	**X**	**X**
Demographics (9 items)	**X**	
**Total number of self-report items per timepoint**	**48**	**17**

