#### Secondary outcome measures

We will use standard telephone interviews with patients to collect secondary outcomes measures 1 week (T1) and 1 year (T2) after the initial recruitment consultation. These include: screening intention (1 item, assessed at T1), knowledge about the test instructions and the objectives of the screening test, (2 items, assessed at T1 and T2), patient activation (13 items- assessed at T1 and T2). We will use a validated short form patient activation measure, already available in French [43, 44]. We will assess HL using the Newest Vital Sign [45] (6 items) and the “single item literacy screener” [46] (1 item) (both assessed at T1). We will evaluate decisional conflict with SURE (4 items, assessed at T1) [47]. Finally, we will assess the proportion of patients who complete colonoscopy after a positive FIT test result within 1 year (collected by each regional coordination center in collaboration with the health insurance body). We will also collect socio-demographic information: age, gender, comorbidities, mother tongue, marital status, length of time living in France, educational attainment, income bracket, whether help was required to complete the questionnaire, any previous screening tests completed and the EPICES (Évaluation de la Précarité et des Inégalités de santé dans les Centres d’Examens de Santé), a validated measure of deprivation and social health in French, with 11 self-reported items (assessed at T1) [46].

Secondary outcomes for GPs will include a translated 12-item questionnaire assessing self-reported HL knowledge, skills, and behavior, collected prior to the intervention training and 1 year post training for GPs in both trial arms. We will also collect demographic information: age, gender, type of practice (GP practicing alone or in a medical center), year of medical training and participation in (and details of) a lump-sum participation package, ROSP (la rémunération sur objectifs de santé publique), an incentivized public health initiative. Tables 1 and 2 summarize the outcome measures and data collection timepoints.

**Table 2 Tab2:** Outcome measures and data collection timepoints for GPs

Outcome measures	Timepoints	
	Immediately before the health literacy training	1 year after the health literacy training
Health literacy knowledge, skills, and behavior (12 items)	**X**	**X**
Demographics (6 items)	**X**	
**Total number of self-report items per timepoint**	**18**	**12**

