### Statistical analysis

Initial examination of data will include descriptive statistics, frequency distributions, and histograms to identify outliers and missing data. The baseline data in each arm will be compared to ensure randomization was conducted successfully. We will use the Stata 16 software (Stata corp, US) to perform all analyses.

All participants will be asked to indicate at T1 if they have received the intervention to enable an intention-to-treat (ITT) and as-treated analysis. We will adopt a regression framework for all analyses as it allows seamless transition between basic analyses involving a single predictor and more complex analyses involving additional predictors (mediation variables, control covariates, time-trends, interaction terms or effect modifiers).

Further, the regression framework allows clustering of observations due to repeated measurements on patients across time, nesting of health professionals within sites, and patients within health professionals, to be accurately accounted for using mixed-effect regression models [53] or generalized estimating equations [54, 55].

### Analyses corresponding to aim 1

We will first perform separate analyses for each data collection period (T1 and T2) using linear and logistic regression models as appropriate for continuous (knowledge, patient activation, HL), and binary (screening intention, screening uptake, colonoscopy completed) outcomes respectively. The results will provide potentially valuable insights into how rapidly the intervention affects outcomes. Outcomes measured twice may also be analyzed using a longitudinal model. A secondary analysis that adds predictors for the number of patients seen by the healthcare professional in the intervention arms will examine whether there are physician learning effects. To gain insight into whether the intervention will be more effective according to the patient’s HL level and socioeconomic position, we will test the first order interaction between HL level/socioeconomic position and the intervention indicator variables. EPICES scores will also be used.

### Analyses corresponding to aim 2

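### Health literacy measured a week after exposure is labelled baseline and serves as both outcome and moderator; colonoscopy after a positive FIT is to be modelled in a very small group selected by uptake; and the ITT wording leans on reported receipt

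*Protocol article*

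**What the plan says.** **Health literacy.** Hypothesis 1.2 states "HL level at baseline (T1) and socioeconomic position will affect screening uptake and moderate" the intervention's effect. Table 1 heads the T1 column "T1) One week after the primary care consultation where CRC screening is discussed" and shows health literacy (7 items) at T1 only. Under Ethical approval, consent and recruitment strategies, patients of intervention GPs "will be given a pictorial brochure about CRC screening and asked to watch a 3-min video on a tablet before exiting" the practice, and then "One week after (T1), the CRA will call participants and offer to conduct a standardized telephone interview". GP recruitment says GPs are allocated "prior to the intervention training process, 2 months before patient recruitment begins". Analyses corresponding to aim 1 applies regression to "continuous (knowledge, patient activation, HL), and binary (screening intention, screening uptake, colonoscopy completed) outcomes", and later in the same paragraph tests the interaction of health literacy with arm.

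**Colonoscopy.** Secondary outcome measures says "we will assess the proportion of patients who complete colonoscopy after a positive FIT test result within 1 year", using data from the regional centres and the health insurer. It is one of the outcomes in Hypothesis 1.1, it is on the logistic list just quoted, and Hypothesis 1.2 expects the effect on it to be mediated.

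**Receipt.** Statistical analysis has all participants report at T1 whether they received the intervention, "to enable an intention-to-treat (ITT) and as-treated analysis".

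**The concern.** In each case the plan conditions on something observed after the intervention has begun.

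- A moderator should be fixed before exposure. If the intervention moves it, the strata of high and low literacy hold different kinds of patient in the two arms, and the interaction mixes effect modification with the effect on literacy itself. Listing the same variable as an outcome says that such an effect is at least being looked for. The T1 measure also feeds the mediation subgroups and the section on heterogeneity of treatment effect.
- Patients with a positive FIT are patients who took the test. If the intervention raises uptake, the FIT-positive groups in the two arms are selected differently, and allocation no longer makes them comparable. If they are also very few, a clustered logistic model and a mediation analysis cannot give a useful answer to a named part of Hypothesis 1.1.
- ITT needs only the allocated arm. Wording that makes it rest on a question about receipt invites the wrong analysis set. Grouping by reported receipt is also unsound here because the intervention has two parts: an intervention patient who reports no brochure or video still saw a GP allocated to the training.

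**Working it through.** **Timing of health literacy.** The order of events in the document is:

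1. GPs are allocated before training, two months before patient recruitment (GP recruitment).
2. The patient sees the GP, receives the brochure and is asked to watch the video before leaving (Ethical approval, consent and recruitment strategies).
3. One week later, T1: Newest Vital Sign (6 items) and single-item literacy screener (1 item) (Secondary outcome measures).

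Table 1 has no patient questionnaire before T1. Health literacy is therefore measured after exposure, and the word baseline in Hypothesis 1.2 is wrong. Analyses corresponding to aim 1 puts it on the left of one model (continuous outcome) and on the right of another (interaction with arm). Both follow from the text without arithmetic.

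**Number of FIT-positive patients.** The document gives no FIT positivity and no expected count, so there is no figure of its own to reproduce. Inputs:

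- N = 32 GPs x 32 patients = 1024, which matches the abstract; 512 per arm, assuming equal arms.
- Control uptake 30.5%: the national rate from the Background, assumed to apply to these patients.
- Intervention uptake 45.5%: 30.5% plus the 15% difference in the sample size section, read as percentage points.
- FIT positivity: assumed, 2% to 10%.
- No loss for attrition, because the data come from regional records.

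Screened: 512 x 0.305 = 156.2 and 512 x 0.455 = 233.0, in total 389.1. Positives = screened x positivity:

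| Positivity (assumed) | Control | Intervention | Both arms |
|---|---|---|---|
| 2% | 3.1 | 4.7 | 7.8 |
| 3% | 4.7 | 7.0 | 11.7 |
| 4% | 6.2 | 9.3 | 15.6 |
| 6% | 9.4 | 14.0 | 23.3 |
| 10% | 15.6 | 23.3 | 38.9 |

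If the 25% attrition in the sample size section did apply (N = 768), 3-6% positivity gives 8.8 to 17.5.

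**Precision.** With completion 85% in both arms (assumed), the variance per patient is 0.85 x 0.15 = 0.1275. The 95% half-width is 1.96 x sqrt(0.1275/n1 + 0.1275/n2):

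- 4% positivity: 1.96 x sqrt(0.1275/6.2 + 0.1275/9.3) = 0.36, about 36 points.
- 10% positivity: 1.96 x sqrt(0.1275/15.6 + 0.1275/23.3) = 0.23, about 23 points.

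The normal approximation is only indicative at these counts, and clustering is ignored. On the same footing, power to separate 70% from 90% completion is about 15% with 5 v 7 patients and about 24% with 9 v 14.

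**Receipt.** ITT is defined by allocation, which is known for every patient through the GP (Randomization). No T1 answer enters it. The sentence in Statistical analysis therefore links ITT to a variable that it does not use.

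**The case against.** The strongest reply is that little of this reaches the main result. Uptake by allocated arm is untouched. The legend to Fig. 2 calls mediation and moderation exploratory, and the section on heterogeneity says much the same. ITT stands beside as-treated. All of that is correct, and it limits the weight of the point.

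Four stronger readings are tempting and are not supported:

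- A reader might infer that the literacy moderation result would be uninterpretable. The documents do not show that a brochure and a 3-minute video shift these scores within a week. Health literacy is also absent from the effects listed in Hypothesis 1.1. If the score does not move, comparisons within literacy strata keep the protection of allocation. What is certain is the wrong label and the double role, not a bias of known size.
- A reader might take 12 to 23 FIT-positive patients as fact. That range holds only for an assumed 3-6% positivity and the national uptake rate. FIT-positives are also the natural denominator rather than one spelled out. The conclusion that the group is very small holds across the wider range.
- A reader might expect as-treated to create a false effect of some stated number of points. The document gives no regrouping rule, no recall rate and no uptake among patients who do not recall, so no such figure can be derived.
- A reader might want a complier-average effect with arm as the instrument, or a completed-screening composite in place of colonoscopy. The first fails because arm also acts through the trained GP, so allocation affects uptake other than through recalled receipt. The second would be about 96% negative FITs at 4% positivity and would nearly repeat the primary outcome.

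EPICES and education are also collected at T1, so they do not offer a pre-exposure alternative.

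**Conclusion.** The point holds in limited form. Health literacy at T1 is not baseline and should not be both outcome and moderator; this is an inconsistency in the text, and the size of any resulting bias is unknown. Colonoscopy after a positive FIT is not a comparison protected by randomisation, and it would rest on about 8 to 39 patients in both arms together (2-10% positivity; 12 to 23 at 3-6%). Precision would be about ±36 points at 4% positivity and 85% completion. These figures assume 30.5% v 45.5% uptake, 1024 patients in equal arms, no attrition and no clustering. Logistic regression and mediation are not useful at these counts. The sentence on receipt needs correcting because ITT does not depend on it. The primary ITT analysis of uptake is unaffected, so this is a correction that should be made, not an obstacle to the trial.

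**What to change.** 1. **Health literacy.** Correct the label in Hypothesis 1.2 and take health literacy off the outcome list in Analyses corresponding to aim 1. Ask the existing single-item literacy screener before the brochure, the video and the discussion of screening, and make it the main literacy moderator. Keep the T1 Newest Vital Sign, EPICES and education as moderators only if they are described as measured after exposure and assumed unaffected, with their distribution reported by arm.
2. **Colonoscopy.** State the denominator. Report completion after a positive FIT by arm as counts with exact intervals, say that it is not a randomised comparison, and remove it from the logistic and mediation analyses.
3. **Receipt.** State that ITT uses the allocated arm and does not depend on reported receipt. Drop as-treated or label it descriptive, and do not replace it with a complier-average effect based on recalled receipt.

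The cost is mostly wording. The one practical change is a single question at enrolment. It has to be asked in the same way in both arms, by practice staff who may know the allocation. The remark under Randomization that GPs need not assess health literacy should be squared with it, for example by having another staff member ask. No new data source is needed.
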